## Trial status

Recruitment to the SIMPLIFIED trial commenced in March 2017, but has experienced significant delays due to the COVID-19 pandemic. The study is now active in 55 UK renal units. The current protocol is version 11.0 dated 6th February 2025. As of 1 st May 2025, 3800 patients have been recruited. Recruitment is expected to close in Q3 2025 and follow-up be completed by the end of Q4 2025. Analysis is planned for Q2 2026.

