**Methods:**

The SIMPLIFIED (Survival Improvement with Cholecalciferol in Patients on Dialysis) trial will test whether supplementation with high-dose cholecalciferol improves survival. Adult dialysis patients will be recruited from one of 72 UK renal centres, by local clinicians and research nurses, and randomly assigned in a 1:1 ratio to high-dose open-label cholecalciferol or standard care, stratified by site. Trial outcomes will be captured using existing data sources including Office of National Statistics (ONS) for deaths and Hospital Episode Statistics (HES) for secondary endpoints. The primary endpoint of the trial is all-cause mortality. Key secondary endpoints include survival free from cardiovascular events, infections and cancers, and quality of life and cost-effectiveness measures utilising the Eq5D tool. Severe adverse event line listings will be generated from HES data for safety reporting. In this superiority trial, it is anticipated that approximately 4200 patients in total will need to be enrolled to observe 2200 deaths over a period of about 7 years, which will yield 90% power to demonstrate a hazard ratio of 0.87.

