### Sample size {14}

The SIMPLIFIED study is an event-driven trial. It is estimated that the control arm has a 3-year survival of 68% [1]. It is estimated that randomisation of 4200 patients would yield 2200 primary outcome events (deaths) over 7–8.5 years, resulting in 90% power at 5% significance (two-sided) assuming a hazard ratio of 0.87. Dropout is assumed to be negligible given the national death registry data source for primary endpoint collection.

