## Statistical methods

### Statistical methods for primary and secondary outcomes {20a}

#### Primary outcome analysis

The primary efficacy analysis will be by intention-to-treat comparing patients randomised to cholecalciferol and those randomised to receive standard of care, adjusted for baseline characteristics including age, gender, diabetic status and length of time on dialysis. SIMPLIFIED is an event-driven trial and will continue until 2200 events (deaths) have occurred. Prior to the primary analysis, survival status will be confirmed by cross-referencing UKRR and ONS data. For participants where no death has been recorded by either ONS or the UKRR at the end of the trial, follow-up time will be censored at the point of last known follow-up. Last known follow-up will be defined as whichever is most recent of either the date of last recorded UKRR-submitted dialysis results or last 6-monthly questionnaire follow-up. The primary analysis will be carried out after the occurrence of 2200 events, using Cox proportional hazards regression modelling to test the effects of randomisation to cholecalciferol on all-cause mortality. The survival times will be summarised using Kaplan–Meier curves. All estimates of hazard ratios associated with treatment and baseline covariates will be provided with 95% confidence intervals and *p* values.

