### Interim analyses {21b}

A feasibility assessment will be carried out between months 12 and 15 of the trial. Feasibility will be predicated on recruitment rate (target 887 patients recruited after 12 months), and separation between arms by plasma vitamin D concentration after 4 months of treatment of 20 nmol/l.

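### On the trial's own planning figures, follow-up ending in Q4 2025 is not expected to yield 2200 deaths, so the stated dates conflict with the event-driven rule

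*Protocol article*

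**What the plan says.** Three parts of the protocol article bear on when follow-up ends.

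- **The rule.** Primary outcome analysis: "SIMPLIFIED is an event-driven trial and will continue until 2200 events (deaths) have occurred". The same section places the primary analysis after those 2200 events.
- **The planning basis.** Sample size: "It is estimated that the control arm has a 3-year survival of 68% [1", and "randomisation of 4200 patients would yield 2200 primary outcome events (deaths) over 7–8.5 years, resulting in 90% power", for a hazard ratio of 0.87 at two-sided 5%, with dropout taken as negligible. The abstract gives a shorter duration: "to observe 2200 deaths over a period of about 7 years". Interim analyses sets a feasibility benchmark: "target 887 patients recruited after 12 months".
- **The dates.** Trial status reports a March 2017 start, pandemic-related delay and 3800 patients recruited by 1 May 2025. It then says: "Recruitment is expected to close in Q3 2025 and follow-up be completed by the end of Q4 2025". Analysis is planned for Q2 2026. The section gives no death count and does not make the dates conditional on 2200 deaths.

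**The concern.** The planned duration assumed recruitment fast enough to leave several years of follow-up for most patients. In fact the first 3800 patients took 8.2 years to enrol, and follow-up is to end about three months after recruitment closes. Patients who enrolled late contribute few deaths by then, so the end of 2025 lies close to the planned total duration but not obviously close to the planned number of deaths.

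At stake is which rule ends the trial. If the death count governs, the published dates are too early on the plan's own assumptions. If the calendar governs, the analysis is done on fewer deaths than the power statement assumes, and a null result would be less informative than readers are told. Patients and investigators know individual allocations, so the trigger for the primary analysis should be unambiguous.

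**Working it through.** **1. The event target reproduces.** Schoenfeld's formula with 1:1 allocation:

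4 × (1.960 + 1.282)² / (ln 0.87)² = about 2167 deaths.

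Power at 2200 deaths is Φ(√(2200/4) × 0.1393 − 1.960) = 90.4%. The target and the stated power agree.

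**2. Hazards.** Control: −ln(0.68)/3 = 0.1286 per year. Cholecalciferol: 0.87 × 0.1286 = 0.1118 per year. A constant hazard is my assumption; the article gives only the 3-year figure.

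**3. Deaths by 31 December 2025.** For patients entering evenly, with follow-up between *a* and *b* years, the expected proportion dead is

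1 − (e^(−ha) − e^(−hb)) / (h(b − a)).

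Uniform accrual of 3800 from March 2017 to 1 May 2025 gives *a* = 0.667 and *b* = 8.833:

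- control 0.432, cholecalciferol 0.391, so 1900 × (0.4317 + 0.3915) = 1564 deaths;
- a further 400 patients by the end of Q3 2025 (*a* = 0.25, *b* = 0.667) add 200 × (0.0571 + 0.0499) = 21 deaths;
- total about 1585.

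Power for hazard ratio 0.87 is Φ(√(1585/4) × 0.1393 − 1.960) = 79%. The hazard ratio detectable with 90% power is exp(−2 × 3.2415/√1585) = 0.85.

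**4. Sensitivity to the accrual curve.** The article does not give the curve, so I varied it. Each row credits 3800 by 1 May 2025 and 400 more by the end of Q3 2025.

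| Assumed accrual of the first 3800 | Deaths by end 2025 | Power | 2200th death | 3-year control survival needed for 2200 by end 2025 |
|---|---|---|---|---|
| 800 in first 3 years, rest evenly | 1424 | 75% | late 2028 | 47% |
| 40% in first half of the period | 1478 | 76% | mid-2028 | 49% |
| Uniform | 1585 | 79% | early 2028 | 52–53% |
| 60% in first 3 years | 1825 | 84–85% | mid-2027 | 60% |
| 887 a year for 3 years, then evenly | 1928 | 86% | early 2027 | 62% |
| 887 a year until 3800, then none until May 2025 | 2100 | 89% | mid-2026 | 66% |

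The last row is the fastest curve possible if the first 3800 enrolled at no more than 887 a year. With no treatment effect (hazard ratio 1) it gives 2195 deaths; uniform accrual gives 1663.

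**5. The planned duration.** At 887 a year, 4200 patients take 4200/887 = 4.7 years to enrol.

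| Time from start | Deaths, hazard ratio 0.87 | Deaths, hazard ratio 1 |
|---|---|---|
| 7 years | 1759 | 1849 |
| 8.5 years | 2160 | 2261 |

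The upper end of the range in Sample size works at that rate; 7 years does not. Reaching 2200 deaths by year 7 would need all 4200 randomised within about 1.6 years (2.4 years if the hazard ratio is 1).

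**The case against.** The strongest reply is that the Trial status dates are a forecast, worded as an expectation, while the stopping rule is stated firmly elsewhere and nothing withdraws it. That stands. A reader might infer that the trial has lost its 90% power or has abandoned its event target. The article supports neither: power is tied to 2200 deaths, and it falls only if the calendar date overrides the rule.

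A reader might also infer that 2200 deaths by the end of 2025 is impossible. That goes too far as well, for three reasons.

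- The recruitment curve and the death count are not published, and the most front-loaded curve comes close to the target. However, it requires no enrolment from mid-2021 to May 2025. That fits poorly with remote consent being introduced in September 2021 to help recruitment, and with recruitment still open in 2025.
- Mortality may exceed the planning figure. Background and rationale reports that fewer than 40% of dialysis patients aged 65 and over survive 4 years. At exactly 40% the hazard is −ln(0.40)/4 = 0.229 per year. Applied to every control patient, with the treated hazard at 0.87 of it, this gives about 2280 deaths under uniform accrual. It is an illustration only, since not all patients are that old and Sample size does not plan on that rate.
- Deaths arrive in regular data tranches, so the forecast may rest on an observed count. The article does not say so, and this can be neither confirmed nor excluded.

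Finally, the gap between 3800 and 4200 recruits is not a second contradiction. Trial status gives a closing date and does not say that 4200 will be reached. The last 400 patients add only about 21 deaths.

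**Conclusion.** The dates in Trial status and the rule in Primary outcome analysis conflict on the trial's own figures. Under uniform accrual the shortfall at the end of 2025 is about 615 deaths (2200 − 1585), or 28% of the target. It ranges from about 100 to about 780 across the accrual shapes tested. None of these shapes reaches 2200 by that date at hazard ratio 0.87.

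The result rests on a constant hazard from the 68% figure, negligible dropout, and accrual of the first 3800 shaped by assumption. The 887-a-year ceiling extends a first-year feasibility target, because later planned rates are not stated. Higher mortality than planned could rescue the dates, but the article offers no count to show it. The event target and its 90% power are correct as stated. What is wrong is that the article gives two end points that do not agree and does not say which one governs.

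The abstract's duration fails separately at the 887-a-year rate, by about 350 to 440 deaths at 7 years. This is a smaller matter, since Sample size already carries the longer range.

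**What to change.** 1. In Trial status, give the pooled death count to date (both arms combined) and state that the 2200-death rule governs the end of follow-up and the primary analysis.
2. Re-project the end-of-follow-up and analysis dates from that pooled count. If the count shows that 2200 deaths by the end of 2025 is realistic, saying so resolves the conflict.
3. If the calendar end is binding, say so, and restate the expected deaths, the power for hazard ratio 0.87 and the detectable hazard ratio (about 0.85 at roughly 1580 deaths).
4. In the abstract, replace the duration of about 7 years with one that matches Sample size and the recruitment it assumes.

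The cost is a few sentences and one projection from pooled data, which reveals nothing by arm. If follow-up has to run longer, the price is later linkage extracts and a later analysis. The Discussion already describes extended follow-up through routine data as very cost-effective, and no extra patients are needed.

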## Data Availability

When the database from the trial is locked, analysed and published, we will endeavour to make data available upon reasonable request and pursuant to contractual agreements*.*

## Abbreviations

ACS: Acute coronary syndrome
C&C: Capacity and capability
CCTU: Cambridge Clinical Trials Unit
CEA: Cost-effectiveness analysis
CUA: Cost-utility analysis
CHI: Community Health Index
CKD: Chronic kidney disease
eCRF: Electronic case report form
eDRIS: Electronic Data Research and Innovation Service
Eq5D: Euro-Qol 5 Dimension
ESKD: End stage kidney disease
HES: Hospital Episode Statistics
HRQoL: Health-related quality of life
HTA: Health Technology Assessment
ISRCTN: International Standard Randomised Controlled Trial Number
KDIGO: Kidney Disease Improving Global Outcomes
MHRA: Medicines Health and Regulatory Authority
NHS: National Health Service
NIHR: National Institute of Health Research
ONS: Office of National Statistics
PI: Principal investigator
PID: Personal identifiable data
REC: Research Ethics Committee
SAE: Serious adverse event
SAIL: Secure Anonymised Information Linkage
SAR: Serious adverse reaction
SUSAR: Suspected unexpected serious adverse event
UK: United Kingdom
UKRR: UK Renal Registry
